### Participant timeline {13}

The participant timeline is shown in Table 1.

**Table 1 Tab1:**
[figure not shown]
Participant timeline

### Sample size {14}

In total, we require 1400 eligible patients (70 per practice) from 20 general practices to provide 80% power with two-sided 5% significance level to detect a 10% increase in bowel screening participation in the intervention group compared to the control group (50% vs 40%). The estimates are based on average general practice population size, assuming an intra-cluster correlation of 0.008 based on previous studies in general practice [34]. We have not allowed for attrition as the primary outcome data will be collected from the EMR and we anticipate no loss of practices because of the minimal requirement of input from general practice staff.

We aim to recruit up to 20 practice staff and 20 patients (or until data saturation is reached) from the intervention group for the interviews.

### Recruitment {15}

Potentially eligible general practices will be identified through VicRen, the University of Melbourne Department of General Practice research and education network [35]. The trial coordinator will recruit purposively to ensure a diverse sample by rurality and size of general practice is achieved. All participating general practices will be reimbursed $AUD 500 for their involvement in the trial in recognition of the administrative costs involved in participation.

Recruitment of interviewees is described previously.

## Assignment of interventions: allocation

### Sequence generation {16a}

The unit of randomisation (cluster) will be the general practice. Once consented, general practices will be randomly allocated with a 1:1 ratio to either the intervention or control group. Using a computer-generated allocation sequence, stratified by geographical remoteness (two strata defined below) and general practice size (< 1000 patients vs ≥1000 patients), with random permuted block sizes within each stratum. Geographical remoteness will be classified using the Modified Monash Model (MMM) classification [36], as either metropolitan/regional cities (MMM 1-3) or rural town/remote communities (MMM 4&5) General practice size will be determined by the number of active patients aged 50 to 60 years old.

### Concealment mechanism {16b}

To ensure concealment the block sizes will not be disclosed. The statistician will be blinded to the allocation of the general practices using a code of 1 and 2 for the two trial groups in the generated allocation sequence. The key to the code for the trial groups will be retained by the study coordinator. Once the practice has been informed about the allocation, the trial coordinator will record the practice’s code and trial group allocation but will not report the allocation to the statistician.

### Implementation {16c}

A statistician who is blinded to the identity of the participating general practices and not involved in the trial recruitment and data collection will generate the allocation sequence. The statistician will inform the trial coordinator of the randomisation outcome of each general practice who will inform the practice manager of their general practice trial allocation both in writing and verbally.

## Assignment of interventions: Blinding

### Who will be blinded {17a}

General practice staff and patients cannot be blinded to the study group allocation due to the nature of the intervention. The statistician and investigators not involved in the delivery of the intervention will remain blinded to the study group status using a code. The key to the code will be securely stored by the trial coordinator.

### Procedure for unblinding if needed {17b}

The study group status code will only be revealed to the investigators and statistician after all the primary outcome data have been collected and the results presented to the investigators.

## Data collection and management

### Plans for assessment and collection of outcomes {18a}

Demographic data collected at baseline will describe each general practice by size, determined by the number of patients aged between 50 and 60 years old and the location of the general practices as classified using the Modified Monash Model [36]. Data collection will be undertaken at the general practice by the practice manager. Data will be collected from the CAT4 clinical audit tool and using the SMARTscreen filters. These data include the number of eligible patients in each age group (50, 52, 54, 56, 58, 60 years old); their sex; if they have a mobile telephone number recorded and if they have opted out of receiving SMS messages from the general practice. Each general practice staff member participating in the SMARTscreen trial will be trained to apply the filters, use CAT4 and collect these data. Data will be collected monthly in intervention general practices and at two 6-monthly time points in control group general practices. Data collection related to the use of the SMS intervention will be automatically collected by GoShare Plus and is the number of SMS sent; the number of SMS opened and the number of times each of the four intervention components are viewed. All data will be de-identified for each age group (50, 52, 54, 56, 58, 60 years old) and sex (male/female/other) by the general practice.

Qualitative data will be collected from semi-structured interviews. All interviews will be audio-recorded and transcribed verbatim using a University of Melbourne preferred transcribing agency. All transcripts will be anonymized.

### Plans to promote participant retention and complete follow-up {18b}

The trial coordinator will be in regular contact with the general practice staff in the intervention group throughout the 6-month period when they are sending out the SMSs. This will ensure any troubleshooting of problems are managed immediately and also ensure the fidelity of the intervention and data. During this time the trial coordinator will keep records of any deviations from the trial or problems encountered which will be included in the results as part of the process evaluation.

### Data management {19}

All data will be collected by the trial coordinator from the general practices and from Healthily. All data will be de-identified and aggregated. Data management will be done by the trial coordinator and all de-identified data will be stored on University of Melbourne password protected computers with a secure two-factor authentication for extra security.

### Confidentiality {27}

All research data collected will be stored in accordance with the University of Melbourne’s Research Data Management Policy and Research Code of Conduct. Any identifiable data such as consent forms will be stored on the University of Melbourne managed storage infrastructure which are password protected and restricted.

All interview data will be presented after analysis and will not include any identifying information. Participants will be represented by pseudonyms and combined characteristics when using examples so they cannot be identified. All data will be destroyed 5 years after publication according to the University of Melbourne Office of Research Ethics and Integrity Ethics Committee (OREI)

### Plans for collection, laboratory evaluation and storage of biological specimens for genetic or molecular analysis in this trial/future use {33}

Not applicable. No biological specimens were collected.

## Statistical methods

### Statistical methods for primary and secondary outcomes {20a}

Descriptive statistics will be used to summarise the general practice characteristics, patients age and sex for both trial groups. We will also compare the proportion of active patients aged 50 to 60 years old and due to a NBCSP kit that was excluded because they did not have a mobile telephone number recorded in their EMR record, or opted out of receiving SMS messages from their general practice.

Intention-to-treat analysis will be used, where all general practice allocated to the trial group will be included and analysed in the group they were assigned [37]. The primary outcome will be calculated as the proportion of eligible patients who complete the FOBT up to 12 months following the beginning of the trial intervention for both the intervention and control groups. The primary outcome will be compared between the intervention and control groups using logistic regression and generalised linear model with an identity link function and binomial family to estimate the odds ratio and difference in proportions, respectively. Both regression models will use generalised estimating equations with robust standard errors to allow for clustering by general practice and will adjust for the randomisation stratification factors (geographical remoteness using the Modified Monash Model) and general practice size. Both the relative and absolute measures of the estimated intervention effect will be reported with respective 95% confidence intervals, and a *p* value calculated from the logistic regression model. The intra-practice correlation, which quantifies the proportion of the total variation in the outcome attributable to between-cluster variation in the outcome, will also be estimated using one-way analysis of variance and reported with 95% confidence intervals. Statistical analysis will be conducted using Stata statistical software 15 [38]. Process measures will be summarised as counts and proportions of active patients who opened each of the four intervention components of the SMARTscreen intervention SMS at least once, and how many of the components were opened (none, 1, 2, 3 or 4). We will also summarise the number of times the links to the four interventions were accessed.

Qualitative acceptability and feasibility outcomes will be described by themes from the inductive analysis of interviews with general practice staff and patients.

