## Introduction

### Background and rationale {6a}

Australia and New Zealand have some of the highest rates of colorectal cancer (CRC) in the world [1]. In 2019, CRC was the fourth most commonly diagnosed cancer and the second commonest cause of cancer death in Australia. Currently, 40% of CRC is diagnosed at a late stage, leading to a poorer prognosis and outcome [2]. The simplest and most cost-effective method for reducing mortality from CRC is to detect precancerous or early disease through screening with a self-collected immunochemical faecal occult blood test (‘FOBT’) [3].

The Australian Government implemented a National Bowel Cancer Screening Program (NBCSP), sending people aged between 50 and 74 years a free home-based FOBT test kit every 2 years [4]. Despite the ease of access to the NBCSP testing kit, participation is low; only 44% of people return the completed kit. Women are more likely to complete the kit than men (46% compared with 41%) and older people are more likely to complete the kit than younger people (54% of 70 to 74 years old compared with 34% of 50 to 54 years old) [5]. Increasing participation in the NBCSP is a major Australian Government Health Department priority and has potential to significantly reduce morbidity and mortality associated with CRC as well as reduce unnecessary costs [6]. An increase in uptake of screening from 44 to 60%, will prevent 37,300 bowel cancer cases and 24,800 bowel cancer deaths and increasing participation in the NBCSP from 40% to 60% is estimated to reduce annual expenditure associated with CRC by a cumulative $AUD 1.7 billion up to 2030 and $AUD 2.1 billion between 2030 and 2040 [6].

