These single interventions have had small effects on screening uptake [16, 19, 20]. This trial tests a combination of the four interventions within a single SMS (the ‘SMARTscreen intervention’) including (1) a GP endorsement of CRC screening, (2) video stories from relatable people who have had a positive experience about doing the test, (3) an advance notification video about how to complete the FOBT kit, and (4) information about the benefits of CRC screening and the NBCSP. The SMS is targeted to patients aged 50 to 60 years directly from their general practice as they are less likely to participate in screening, more likely to use smartphones, and evidence suggests once someone has done the NBCSP kit once, they are more likely to do it again [5]. The SMARTscreen trial aims to test the efficacy, feasibility, and acceptability of sending the SMARTscreen intervention as a prompt to patients prior to receiving their NBCSP kit on uptake of completing the kit.

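### The primary models leave out age and sex, which are counted by practice in both arms, and list source is not recorded: a small, cheap gain in precision forgone, not a bias

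*Protocol article*

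**What the plan says.** The Protocol article, Statistical methods {20a}, specifies a logistic model for the odds ratio and an identity-link binomial model for the difference in proportions. On clustering it says: "Both regression models will use generalised estimating equations with robust standard errors to allow for clustering by general practice". On covariates, the models "will adjust for the randomisation stratification factors (geographical remoteness using the Modified Monash Model) and general practice size". Age and sex appear in that section only as description: "Descriptive statistics will be used to summarise the general practice characteristics, patients age and sex for both trial groups". The section on additional analyses {20b} plans none and says that no further data will be collected.

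Plans for assessment and collection of outcomes {18a} lists what is extracted: "These data include the number of eligible patients in each age group (50, 52, 54, 56, 58, 60 years old); their sex", followed by mobile number recorded and SMS opt-out. The aggregation level is given as: "All data will be de-identified for each age group (50, 52, 54, 56, 58, 60 years old) and sex (male/female/other) by the general practice". Extraction is monthly in intervention practices and at two six-monthly points in control practices.

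Background and rationale {6a} reports 46% completion in women and 41% in men, and an age contrast of "54% of 70 to 74 years old compared with 34% of 50 to 54 years old". It adds that "evidence suggests once someone has done the NBCSP kit once, they are more likely to do it again". Intervention description {11a} describes two CAT4 filters that build the eligible list. One selects by birthday (turning 50, 52, 54, 56, 58 or 60). The other selects patients aged 50 to 60 with an FOBT recorded 24 months earlier.

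**The concern.** The protocol names three predictors of completing the kit: age, sex and earlier completion. It holds counts by the first two in each practice, and one of its filters partly identifies the third. None enters the primary models. The randomisation is stratified by remoteness and practice size only {16a}. With 20 planned practices (21 recruited, per Trial status), the mix of patients can differ between arms by chance. Adjustment for a baseline predictor removes the part of the outcome variation that it explains, and it corrects the estimate for the imbalance that actually occurred. The stakes are therefore the width of the confidence interval and some robustness to an unlucky allocation. The validity of the comparison is not in question.

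**Working it through.** **1. The plan's own figure.** Inputs from Sample size {14}: 40% vs 50%, 80% power, two-sided 5%, 70 patients per practice, ICC 0.008.
- Individually randomised size: 388 per arm without continuity correction, 408 with it.
- Design effect: 1 + 69 × 0.008 = 1.552.
- Practices per arm: 388 × 1.552 / 70 = 8.60, or 408 × 1.552 / 70 = 9.05. The second, rounded up, gives 10 per arm, hence 20 practices and 1400 patients. The stated figure reproduces and relies on no covariate gain.
- Power at 700 per arm: effective size 700 / 1.552 = 451, so Φ{(0.10√451 − 1.96√0.495) / √0.49} = 85.6%. With a t reference on 18 df it is 81.8%.
- Planned standard error: √(0.49 / 700 × 1.552) = 0.033, or 3.3 points.

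**2. Age and sex.** Outcome variance at the average rate of 45%: 0.45 × 0.55 = 0.2475.
- Sex, using 46% vs 41% and assuming an even split: 0.25 × 0.05² / 0.2475 = 0.25%.
- Age: the documents give no gradient within 50 to 60. Reading 34% at 50–54 and 54% at 70–74 as a straight line gives 20 points over 20 years, or 1 point per year. I used 0.5 to 2 points per year. With the six age groups assumed equally common, the variance of age is 11.67 years². At 1 point per year: 0.01² × 11.67 / 0.2475 = 0.47%. Over the range: 0.12% to 1.89%.
- Together: 0.4% to 2.1% (0.7% at 1 point per year).
- Power, dividing the effective size by (1 − R²): from 85.6% to between 85.8% and 86.4%. This equals about 5 to 30 of the 1400 patients.
- Effect of an imbalance: a 10-point difference between arms in the share of women moves the crude difference by 0.10 × 5 = 0.5 points. One year in mean age moves it by 1 point at 1 point per year.

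**3. List source.** The documents give neither the share of patients on the 24-month FOBT list nor its effect on uptake. Assumed: share s of 20% to 40%, gap d in uptake of 20 to 50 points.
- Variance explained, s(1 − s)d² / 0.2475: from 0.2 × 0.8 × 0.20² / 0.2475 = 2.6% to 0.4 × 0.6 × 0.50² / 0.2475 = 24.2%.
- Power on the same basis as step 2: 86.5% to 93.5%.
- A 5-point imbalance in share would move the crude difference by 1.0 to 2.5 points.

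The power figures in steps 2 and 3 assume that a covariate explains the same fraction of variance within and between practices.

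**4. A ceiling from the plan's ICC.** At a 40% rate, ICC 0.008 implies a between-practice variance of 0.008 × 0.24 = 0.00192, an SD of 4.4 points. If practices' list shares had an SD of 10 points and the gap were 50 points, list mix alone would give 0.10² × 0.50² = 0.0025. That exceeds the whole between-practice variance, so that combination does not fit the plan's own ICC.

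**The case against.** The strongest reply is that nothing is wrong. Adjusting for the stratification factors matches the randomisation, and chance imbalance is ordinary sampling error that the practice-clustered standard errors already carry. The sample size also stands without further covariates. All of this is correct, and it limits the point to precision.

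A reader might infer more in three ways.
- **That the omission biases the result.** It does not. With a 10-point SD in share and 10 practices per arm, the difference between arms has an SD of 10 × √(2/10) = 4.5 points, and a 50-point gap turns this into 2.2 points of effect. That shift lies inside the planned 3.3-point standard error and is not additional to it. It also rests on the combination that step 4 rules out.
- **That prior-FOBT status is already extracted in both arms.** The protocol documents it as an eligibility filter. It is neither a listed data item nor an aggregation level.
- **That list source equals prior screening.** As described, the birthday filter takes people turning 52 to 60 without regard to earlier tests, so earlier screeners can be on either list. List source is a proxy, and its gap may be narrower than that between screeners and non-screeners.

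It can also be said that extra covariates are commonly left to a statistical analysis plan, which is not shown here. The protocol does not leave the matter open, however. It states the adjustment set for both primary models and gives age and sex a descriptive role, and that stated choice can be improved.

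**Conclusion.** The point holds as a modest improvement to a valid plan. Age and sex are collected by practice in both arms, the protocol itself relates them to uptake, and they are left out of the primary models. Adding them would recover about 0.4% to 2.1% of outcome variance and less than 1 point of power; the age part depends on the assumed slope. The larger potential gain is from list source, at roughly 3% to 24% of variance. That range rests wholly on the assumed share and gap, and list source would first have to be recorded. A practice-level baseline FOBT rate might also help, but the documents do not show that it can be obtained and any gain is assumed, so it is optional.

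**What to change.** Before the allocation code is broken:
1. Add age (one linear term) and sex to the primary logistic GEE, alongside remoteness and practice size, and say how the third sex category is coded. Eligible and completed counts must be available in the same practice-by-age-by-sex cells, as the aggregation level in {18a} suggests.
2. Obtain the risk difference by standardisation from that model, so that added terms cannot upset the identity-link fit. If a marginal odds ratio is wanted, standardise for that too.
3. In both arms, record eligible and completed counts separately for the birthday filter and the 24-month FOBT filter, state how a patient meeting both is classed, and add list source as a covariate.
4. Optionally, add each practice's baseline FOBT rate if it can be extracted. It uses one practice-level degree of freedom.

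Items 1 and 2 cost analysis wording only, and item 3 costs one further split of the counts. The statistical price is that the odds ratio from the model becomes conditional on the added covariates and should be labelled so. The covariates must be fixed in advance, because choosing them after seeing an imbalance would be post hoc.

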## Conclusion

Increasing participation in the NBCSP is critical to maximise the program’s cost-effectiveness and reduce mortality from bowel cancer in Australia. This trial will inform whether an SMS combined with GP endorsement, information and patient narrative can increase uptake of the NBCSP among 50- to 60-year-old patients. It will provide evidence about the feasibility of implementing this approach in general practice. The results of this feasibility trial will also inform decisions about the need for and design of a larger, multi-state trial of the SMARTscreen intervention to determine its effectiveness and cost-effectiveness and important implementation methods. If successful, we believe the intervention is scalable and easily transferable to other types of cancer screening.

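### The planned one-way ANOVA has no trial-group term, so any effect of the SMS is counted as between-practice variation and the reported ICC is biased upward

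*Protocol article*

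**What the plan says.** In the protocol article, Statistical methods for primary and secondary outcomes {20a}, the intra-practice correlation is described as a quantity "which quantifies the proportion of the total variation in the outcome attributable to between-cluster variation in the outcome", and it "will also be estimated using one-way analysis of variance and reported with 95% confidence intervals". The sentence gives no term for trial group, no estimation by arm and no restriction to control practices. Adjustment for the stratification factors is stated in the same section, but only for the two GEE regression models.

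Under Sequence generation {16a}, the practice is the unit of randomisation: "general practices will be randomly allocated with a 1:1 ratio to either the intervention or control group".

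Under Sample size {14}, the plan is that "we require 1400 eligible patients (70 per practice) from 20 general practices", with rates of 50% and 40%, "assuming an intra-cluster correlation of 0.008 based on previous studies in general practice".

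The Conclusion says that the results will "inform decisions about the need for and design of a larger, multi-state trial of the SMARTscreen intervention".

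**The concern.** Each practice belongs wholly to one arm, so the difference between arms is a difference between practices. A one-way ANOVA with practice as the only factor cannot separate the two sources. Its between-practice mean square holds the natural variation among practices plus the variation produced by the intervention.

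The ICC that matters in a cluster trial is the correlation among patients of the same practice within the same arm. That is the quantity in the design effect, and the quantity for which 0.008 was assumed. The planned estimator targets it only if the intervention does nothing.

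At stake is a secondary but published number. If the SMS succeeds, the report would suggest that the planning ICC was too low even if it was exactly right, and the confidence interval would be shifted along with the estimate. Anyone who took the published figure into the design of a later cluster trial would start from a value that is too high, and would do so in just the situation in which a later trial is most likely.

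**Working it through.** **Inputs (Sample size {14}):** control 40%, intervention 50%, so d = 0.10; ICC 0.008; k = 20 practices; m = 70 per practice; "to provide 80% power with two-sided 5% significance level to detect a 10% increase in bowel screening participation".

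**The plan's own figure.** Without clustering, the usual formula for two proportions gives 388 per arm. The design effect is 1 + (70 − 1) × 0.008 = 1.552. Then 388 × 1.552 = 602 per arm, or 8.6 practices per arm. With a t reference distribution on 2 × (practices per arm) − 2 degrees of freedom, 9 practices per arm give 77.1% power and 10 per arm give 81.8%. Ten per arm, or 1400 patients, is therefore consistent with the stated inputs. The sample size is not in question.

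**Expected one-way ANOVA estimate over all practices.**
- Mean binomial variance: (0.40 × 0.60 + 0.50 × 0.50)/2 = 0.245.
- True between-practice variance within arms: 0.008 × 0.245 = 0.00196.
- Within-practice variance: 0.992 × 0.245 = 0.24304.
- Added by the arm difference: (d²/4) × k/(k − 1) = 0.0025 × 20/19 = 0.00263. This exceeds the quantity being estimated.
- Expected ICC: (0.00196 + 0.00263)/(0.00196 + 0.00263 + 0.24304) = 0.00459/0.24763 = 0.0185, which is 2.3 times 0.008.

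**Design effect at 70 per practice.** 1 + 69 × 0.0185 = 2.28, against 1.55. The ratio is 2.28/1.55 = 1.47.

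**Simulation** (20,000 beta-binomial trials per scenario, 70 per practice, true ICC 0.008; mean estimates):

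| Practices | Effect | One-way, all practices | Within arms |
|---|---|---|---|
| 20 | none | 0.0079 | 0.0079 |
| 20 | 10 points | 0.0185 | 0.0080 |
| 21 | none | 0.0080 | 0.0080 |
| 21 | 10 points | 0.0187 | 0.0081 |

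The rows for 21 practices reflect the number recruited according to Trial status. The bias appears only with an effect, and estimating within arms removes it.

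**Dependence on the inputs** (same formula, 20 practices of 70, control 40%):

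| Effect | True ICC | Expected one-way ICC | Ratio |
|---|---|---|---|
| 5 points | 0.008 | 0.0107 | 1.3 |
| 8.5 points | 0.008 | 0.0156 | 1.96 |
| 9 points | 0.008 | 0.0166 | 2.07 |
| 10 points | 0.008 | 0.0185 | 2.3 |
| 10 points | 0.02 | 0.0304 | 1.5 |
| 10 points | 0.05 | 0.0601 | 1.2 |

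**The case against.** **The text does not say that all practices are pooled.** An ANOVA run separately in each arm, or in control practices only, would fit the sentence, and a statistical analysis plan that is not shown may say so. This is fair as a caution. But the article names a specific estimator with one factor and mentions no step by arm, so pooling is the plain reading, and the remedy is the same clarification either way.

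**The stated definition could be taken literally.** A difference between arms is variation between clusters, so the pooled estimate might be said to meet it. It would still not be the ICC that enters a design effect, nor one to compare with 0.008.

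**A reader might infer that the ICC would be more than doubled as a rule.** The documents do not support that. Doubling needs both a true ICC near 0.008 and an effect of about 9 points or more.

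**A reader might infer that the next trial would be about 47% too large.** That figure is the ratio of the two design effects. It assumes the planned effect, the planned ICC, 70 patients per practice again, and planners who use this one estimate uncorrected. The documents say that the results will inform a larger trial, but never that this ICC will size it.

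**Precision is poor in any case.** With 20 practices, the within-arm estimate has a simulated 95% range of about −0.004 to 0.025, so one trial could not reliably tell 0.008 from 0.0185. This stands, but it does not justify adding an avoidable bias.

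**Conclusion.** The point holds within a limited scope. Read plainly, the stated method gives an ICC and a 95% CI that are biased upward whenever the intervention has an effect. The size is about 0.0185 against 0.008 under the planning assumptions, with equal practice sizes and a common within-arm ICC. It is smaller if the effect is smaller or the true ICC is larger.

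A reader might also infer that the trial's main result is compromised. It is not. The odds ratio, difference in proportions, confidence intervals and p value come from GEE models with robust standard errors, which do not use the ANOVA estimate, and the 1400-patient calculation does not depend on it. What suffers is the reported ICC: it could not be set against the planning value, and it would mislead if used for a later design.

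**What to change.** In Statistical methods {20a}, or in the statistical analysis plan, state that the intra-practice correlation is estimated within trial groups, by a pooled within-arm ANOVA with practice nested in arm, and reported with its 95% CI. The cost is one sentence and one line of code, with no new data and no change to conduct or to the primary analysis.

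Further adjustment for the stratification factors is optional and not needed to correct the error. Two binary stratifiers by two arms make up to 8 cells. With 20 practices that could leave 20 − 8 = 12 between-practice degrees of freedom instead of 20 − 2 = 18, and it would change the quantity estimated. The document does not say whether 0.008 is a stratum-adjusted value.
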